#### Definition and selection of cases

All male or female patients of any age presenting to a study site with confirmed malaria.

*Inclusion criteria:* Positive microscopy for *Plasmodium* infection; documented fever or history of fever in the past 48 h; primarily resided in the study area in the previous 3 weeks; residence can be located and mapped; appropriate informed consent obtained.

*Exclusion criteria:* Previously enrolled as a case (repeat malaria infection); age <4 weeks; subsequent PCR negative for *Plasmodium* spp monoinfection.

Cases will be classified according to PCR confirmation of *Plasmodium* spp monoinfection. Severe and non-severe *P. knowlesi* cases will be defined by whether they meet modified WHO 2010 severe malaria clinical and laboratory criteria as described elsewhere.^17^

#### Definition and selection of community controls

A systematic selection procedure will be used to recruit three community controls for each case matched to the same village. This number of controls was chosen to provide sufficient statistical power to measure exposure effects, while at the same time making the recruitment process feasible logistically. Selection of control households and individuals within these households will be conducted using a validated and pretested random method based on up-to-date Malaysian Public Health Department village maps and household lists. Corroboration of the number of households will be undertaken with local residents, public health officers and village heads, where available. Households will be numbered using either the map and/or the household head of family name. A smartphone application generates a random number corresponding to one of the households. Individuals primarily residing within the selected household in the previous 3 weeks will be numbered and then randomised by the same application. All households within the village and all individuals within that household will have an equal chance of being selected. If the selected individual is not present when the fieldworkers visit the household, then they will return up to three times, which may include an arranged later time on the same day or on subsequent days. This will minimise selection bias related to the higher likelihood of male adults or school age children not being present at the household during the day. If it is not possible to obtain informed consent from a selected individual or if the specified inclusion criteria are not met, another individual within the same house will be selected based on the next randomly generated number. Failing this an alternative household will be selected using the same method.

*Control inclusion criteria:* Appropriate informed consent obtained; agree to finger-prick blood sample; negative blood slide and PCR result for malaria (delayed); primarily resided in the study area in preceding 3 weeks; residence can be located and mapped; no history of fever in previous 48 h.

*Control exclusion criteria:* Previously recruited as a case; previously recruited as a control; member of a previously selected control household; age<4 weeks.

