### Study design

This will be a population-based case–control study conducted in two adjacent districts: Kudat and Kota Marudu in the state of Sabah, Malaysian Borneo (figure 1). Within the study sites, all malaria cases, regardless of parasite species, meeting specified inclusion criteria will be enrolled at the corresponding district referral hospital over a 2-year period. Research fieldworkers will go to the village of the case within 2 weeks of focal case detection and randomly select three community controls who have primarily resided in the village for the past 3 weeks. This will enable matching of the controls with the case by the same geographical area (local village) and preceding minimum time period of exposure risk (3 weeks).

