#### Community controls

Because *P. knowlesi* can be acquired by either sex and at any age,^34^
^39^
^43^
^46^ community controls can provide an accurate representation of the study base population. This enables extrapolation of explored variables to the true population at risk.^53^ Choosing controls with no history of fever minimises possible confounding from any concurrent acute illness. By not choosing hospital controls there is some bias generated in assuming controls enrolled out in the community have the same access to the hospital study site as cases. The choice of community controls may also create bias by assuming that the malaria cases that present to the hospital and are enrolled genuinely account for all malaria cases in the community, that is, the study base population. However, in the current setting, factors that increase the likelihood of ascertaining all cases include (1) mandatory state reporting and hospital referral of malaria cases from government and private clinics; (2) the presence of only a single district referral hospital in each of the two study sites and (3) the provision of free or relatively inexpensive treatment at government health facilities. State Ministry of Health guidelines also dictate that a blood film for malaria should be prepared routinely for any patient who presents to a government health facility with fever.

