#### Matching controls for preceding time exposure

Controls will be enrolled within a 2-week time period following identification of the case. Only individuals who have resided in the study area over a 3-week period prior to the presentation of the matched case will be eligible. This will encompass the prepatent time period of *P. knowlesi* infection of around 9–12 days.^40^ Analysis of potential relationships that vary over time such as seasonal planting or harvesting, other agricultural practices, cultural events or meteorological data will be possible.

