#### Recruitment/sample size

We aim to recruit all cases of confirmed malaria of any species or severity over the study duration from Kudat and Kota Murudu district hospitals. On the basis of current recruitment rates of around 10 malaria cases per month over the last year from both sites, we expect to enrol approximately 240 cases of *P. knowlesi* malaria and an additional 90 cases of malaria due to other species in the period December 2012 to December 2014. For the 330 malaria cases we will recruit 990 matched controls. A recruitment logbook will be kept for all screened cases and controls to document reasons for non-eligibility, which will be included in the analysis. With three controls per case, assuming probability of exposure among controls (Po) is 0.1, and the relative risk (RR) of acquiring *P. knowlesi* malaria in exposed subjects relative to unexposed subjects is 0.3, we will need to study a minimum of 210 *P. knowlesi* cases to be able to reject the null hypothesis that there is no difference between cases and controls (ie, relative risk=1), with 80% power and an α level of 0.05.^54^

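### Cases and controls are held to different residence rules; if a case's matched village is not where they mainly lived, ORs for prolonged forest or plantation stays could be biased upward by an unknown amount

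*Protocol article*

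**What the plan says.** For cases, the inclusion criterion in Definition and selection of cases is "primarily resided in the study area in the previous 3 weeks". The residence must also be one that can be located and mapped. Nothing requires the case to have lived mainly in the village or household to which controls are matched.

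For controls, the Protocol article gives three residence units:

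- Village, in Study design: fieldworkers will "randomly select three community controls who have primarily resided in the village for the past 3 weeks".
- Study area, in Matching controls for preceding time exposure ("Only individuals who have resided in the study area over a 3-week period prior to the presentation of the matched case will be eligible") and again in the formal control inclusion criterion ("primarily resided in the study area in preceding 3 weeks").
- Household, at the selection step in Definition and selection of community controls: "Individuals primarily residing within the selected household in the previous 3 weeks will be numbered and then randomised by the same application".

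Controls are matched to the case's home village, a term used in a section heading and not defined. For a selected person who is out when fieldworkers call, "then they will return up to three times, which may include an arranged later time on the same day or on subsequent days". The stated purpose of the design is that "community controls can provide an accurate representation of the study base population".

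**The concern.** A control should be someone who would have been an eligible case if ill. The household listing decides who has any chance of selection, because the study-area criterion can only be applied to people already numbered. If that listing is narrower than the rule for cases, the control pool is filtered on where people lived during the exposure window and the case group is not.

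The filter would act on what the study sets out to measure. The section on key knowledge gaps names human movement and the duration, frequency and timing of forest exposure. The section on case–control designs names activities within the forest and occupational risk. The planned safeguards would not reach the problem. Return visits serve only people already listed, village matching does not help when the loss is within the village, and conditional logistic regression cannot restore people who were never in the sampling frame.

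**Working it through.** **Step 1: who can be a case, and who can be a control in village V.** Take three residents of V.

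| Resident of V during the 3 weeks | Can be a case? | Numbered as a control in V? |
|---|---|---|
| Lives mainly at home; day work or occasional nights in forest or plantation | Yes | Yes |
| Lives mainly outside the study area | No | No |
| Lives mainly at a forest or plantation site elsewhere in the study area | Yes | No |

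Only the third row is asymmetric, and only if that person, when ill, is matched to V. If they are matched instead to the place where they lived in those weeks, controls come from that place and the asymmetry largely disappears.

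**Step 2: direction.** Let f be the fraction of exposed members of the study base who cannot be drawn as controls, and g the same fraction of unexposed members. Control exposure odds are multiplied by (1−f)/(1−g), so the OR is multiplied by (1−g)/(1−f). This exceeds 1 whenever those living away are more exposed than the rest (f > g). For an exposure that is harmful or has no effect, that is away from the null.

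**Step 3: illustrative size.** The protocol gives no value for f, g or the proportion living away, so every value below is an assumption. The only input from the document is an exposure prevalence of 0.1, from Recruitment/sample size.

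*Extreme case, g = 0.* The multiplier is 1/(1−f), and control prevalence becomes 0.1(1−f)/(1−0.1f).

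| f | Control prevalence | OR multiplier |
|---|---|---|
| 0.1 | 0.09/0.99 = 9.1% | 1.11 |
| 0.2 | 0.08/0.98 = 8.2% | 1.25 |
| 0.3 | 0.07/0.97 = 7.2% | 1.43 |
| 0.5 | 0.05/0.95 = 5.3% | 2.00 |

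*Mixture case, which also loses unexposed people.* A fraction a of the base lives away with exposure prevalence e, and the rest have prevalence 0.1. The base prevalence is P = a·e + (1−a)·0.1, controls have 0.1, and with a true OR of 1 the observed OR is [P/(1−P)]/(0.1/0.9).

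| a | e = 0.5 | e = 0.9 |
|---|---|---|
| 2% | P = 0.108, OR 1.09 | P = 0.116, OR 1.18 |
| 5% | P = 0.120, OR 1.23 | P = 0.140, OR 1.47 |
| 10% | P = 0.140, OR 1.47 | P = 0.180, OR 1.98 |

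If both groups follow the same rule, f = g = 0 and the multiplier is 1. The planned minimum of 210 cases plays no part in this check.

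**The case against.** The strongest reply is that the formal eligibility criteria agree. Cases and controls must both have lived mainly in the study area, and the time-matching section says the same. The strengths and limitations list describes controls as having lived in the case's village over the same preceding period, and Study design presents the matching as one of place and exposure time together. Both fit a reading in which the case's village is where the case lived in those weeks. This stands: the text permits that reading. It does not state it, and the village and household wording remains in conflict with the study-area wording.

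The word *primarily* also keeps day workers and people with occasional overnight trips on the household list. This stands and narrows the exposures affected. Someone living mainly in another listed household can be numbered there if that village is sampled. This stands in part: they are not lost to the study, but they are missing from the matched set in which they would have been a case.

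Finally, this is a condensed article, and the field rule for assigning a case's village may be in the full protocol. That is a reason not to assert that the bias occurred. It does not excuse three control rules within one article.

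A reader might infer that controls are uniformly held to a stricter rule, that anyone who travels or sleeps in the forest is barred as a control, and that the ORs are inflated by 1.25 to 2. The documents support none of this. The formal criteria are the same, short trips do not exclude anyone, and those multipliers come from assumed f with no loss of unexposed people, which is the extreme case.

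**Conclusion.** The residence rules do not match and need to be reconciled. The bias is conditional on a case's matched village not being where the case mainly lived during the 3 weeks. If so, ORs for prolonged forest or plantation stay, and for related movement, are pushed upward. Exposures that do not depend on living away from home for most of the window are not directly affected. The size cannot be derived from the document; the figures above show only how it would scale. The point deserves attention because it bears on the primary question, has a predictable direction and cannot be removed by modelling.

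**What to change.** Reconcile Study design, Matching controls for preceding time exposure, Definition and selection of cases, and Definition and selection of community controls into one residence unit and one 3-week window for both groups. Define the case's matching village as the place the case primarily resided in that window.

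Rewording alone comes late: by June 2014, 189 of about 240 expected *P. knowlesi* cases (189/240 = 79%) and 564 controls were enrolled. So add a sensitivity analysis of the primary ORs, limited to matched sets whose case primarily resided in the matched village or household for the 3 weeks, and report how many sets drop out.

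The cost is some lost case sets and some precision. It also requires the case's place of residence in the window to be on record. The restricted analysis speaks only for people who lived mainly in the matched village, so it shows whether the main results depend on the mismatch and does not estimate the effect of prolonged stays away.

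Numbering all usual household members, including those who lived elsewhere in the study area, would also align the groups. It would weaken the same-village, same-period matching and attach the household survey to a home the person did not occupy, so it is not the preferred change.

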#### Non-matching controls for age/gender

While this would have given additional power to detect differences in exposure risks within these demographics, it was decided that age and gender should be evaluated as potential independent risk factors. This will also allow comparisons between *Plasmodium* spp and with disease severity related to age or gender.

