### Statistical plan

#### Primary

The exposures of interest to be compared between *P. knowlesi* malaria cases (PCR-confirmed monoinfection) and controls will include variables relating to demographic, behavioural and socioeconomic factors, red blood cell polymorphisms and serological and immunological blood markers. Analysis will be per protocol, with ORs (including 95% CIs) for exposure risk between cases with *P. knowlesi* infection and controls calculated by the Mantel-Haenszel method and then compared. Confounding variables will be adjusted for using conditional multiple logistic regression models. Normally and non-normally distributed numerical variables will be analysed using t tests and Mann-Whitney U tests, respectively. An initial analysis will be conducted for cases and matched controls with complete variable data sets. The extent of missing data will be assessed and the sensitivity of results to alternative approaches to imputing missing data will be explored, if considered necessary.

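### Drawing one resident from each equally likely household over-samples people in small households, so odds ratios for household size, and for any exposure that varies with it, need a sampling offset or weights

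*Protocol article*

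**What the plan says.** The section Definition and selection of community controls fixes a two-stage draw. First, "A smartphone application generates a random number corresponding to one of the households". Then, "Individuals primarily residing within the selected household in the previous 3 weeks will be numbered and then randomised by the same application". The section sums this up: "All households within the village and all individuals within that household will have an equal chance of being selected". Its exclusion criteria include "member of a previously selected control household", so a household yields at most one control whatever its size. If the chosen resident does not consent or is ineligible, another resident of the same house is tried before moving to a new house.

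Cases are not sampled by household. Under Recruitment/sample size: "We aim to recruit all cases of confirmed malaria of any species or severity over the study duration".

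Under Community controls, the article says that "community controls can provide an accurate representation of the study base population". Under Non-matching controls for age/gender, "it was decided that age and gender should be evaluated as potential independent risk factors".

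The Statistical plan (Primary) gives Mantel-Haenszel odds ratios, and t and Mann-Whitney tests for numerical variables. It then says: "Confounding variables will be adjusted for using conditional multiple logistic regression models". The article mentions no sampling weight or offset.

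**The concern.** A control series should reflect the exposure distribution of the persons who could have become cases. Equal chances for households, followed by one resident each, give a sample that represents households. People in large households are under-represented among controls but not among cases.

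The imbalance operates inside each village, so matching on village leaves it in place. The one-control-per-household rule prevents it from evening out even in a village that supplies many controls.

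Two kinds of result are at stake. Household size is affected directly. Age, which was deliberately left unmatched so that it could be estimated, is affected if age mix differs between small and large households. The same holds for any behavioural or socioeconomic exposure that varies with household size.

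**Working it through.** The article states no figure on this point, so there is none to reproduce. The draw comes from the text. All household distributions below are assumptions.

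**1. Chance of selection.** With H households in the village and m eligible residents in a household, a resident's chance per draw is (1/H) × (1/m). For m = 2 against m = 8 the ratio is (1/2)/(1/8) = 4.

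**2. Replacement within the house.** If each resident consents independently with probability p, a selected house yields a control with probability 1 − (1 − p)^m. A resident's chance is then proportional to [1 − (1 − p)^m]/m.
- p = 0.7: (1 − 0.09)/2 = 0.455 against (1 − 0.3^8)/8 = 0.125, a ratio of about 3.6.
- p = 0.5: (1 − 0.25)/2 = 0.375 against (1 − 0.5^8)/8 = 0.1245, a ratio of about 3.0.

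The 1/m rule is therefore a close approximation and not exact.

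**3. Odds ratios under a true null.** Assume household sizes follow a Poisson distribution truncated to 1–14, with share f(m). Controls then follow f(m), and persons (hence cases under the null) follow m·f(m). Three assumptions for the share of children in a household of size m were used:
- moderate gradient: 0.6(m − 2)/m, zero for m ≤ 2
- strong gradient: (m − 2)/m, zero for m ≤ 2
- no gradient: constant 0.35

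| Assumed mean size | Controls in households ≤3 | Persons in households ≤3 | Null OR, household ≤3 | Null OR child, moderate | Null OR child, strong |
|---|---|---|---|---|---|
| 3.16 | 0.629 | 0.423 | 0.43 | 1.57 | 1.73 |
| 4.07 | 0.423 | 0.238 | 0.43 | 1.39 | 1.57 |
| 5.03 | 0.260 | 0.125 | 0.41 | 1.28 | 1.45 |
| 6.00 | 0.149 | 0.062 | 0.38 | 1.20 | 1.35 |

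Worked example, mean 5.03, moderate gradient: children are 0.366 of persons and 0.311 of controls, so the OR is (0.366/0.634)/(0.311/0.689) = 1.28. With no gradient the child OR is 1.00 at every mean size.

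**4. Which model term repairs it.** Let λ be a person's disease rate given exposures. If controls are drawn with chance proportional to 1/m, the conditional probability that member i of the matched set is the case is λᵢmᵢ / Σₖλₖmₖ. This is conditional logistic regression with offset log(m), coefficient fixed at 1. In a simulation of 30,000 matched 1:3 sets (mean size about 5, larger households holding more children), each pair below is the child OR and the OR per extra household member:

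| Truth | Each entered alone | Both entered | Both entered, plus log(m) offset |
|---|---|---|---|
| 1.00, 1.00 | 1.34, 1.21 | 1.04, 1.21 | 1.00, 1.00 |
| 0.50, 1.00 | 0.67, 1.16 | 0.52, 1.21 | 0.50, 1.00 |
| 1.00, 0.90 | 1.17, 1.10 | 1.03, 1.10 | 0.98, 0.90 |

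Household size as an ordinary covariate largely repairs the child OR, but its own coefficient absorbs the sampling fraction. In the last row a truly protective 0.90 appears as 1.10. The offset repairs both.

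**5. At the planned size.** The article expects about 240 *P. knowlesi* cases. In simulations of 240 sets with assumed mean household size of about 5 to 5.5 and no true age effect, the uncorrected child OR averaged 1.26 to 1.35 and was nominally significant in about 20% to 41% of runs. With the offset, it averaged 0.99 to 1.01, with 4% to 5% significant.

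**The case against.** The strongest reply has four parts.

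First, the selection sentence correctly describes two stages and does not promise every villager the same chance. The representativeness statement argues for community over hospital controls and says only what such controls can provide. That is fair as to intent. However, the article goes on to rest extrapolation to the population at risk on these controls, and the draw it specifies does not sample persons evenly.

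Second, this is a condensed article. It does not list its confounders, and a full protocol or analysis plan might contain weights or an offset. A reader might infer that the study has no correction at all. The article cannot show that, and its silence is not the fault. The point rests on the stated draw set against the stated representativeness, and on the stated analysis giving biased results if followed as written.

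Third, the age bias is conditional. A reader might infer that age odds ratios are certainly wrong, or that children and poorer families are known to be under-represented. The article gives no household sizes, no age mix by household size and no link between household size and poverty. If age mix is unrelated to household size, the child OR is unaffected. Forest, plantation and monkey-contact exposures were not quantified here, and their bias may be small.

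Fourth, same-house replacement means that selection is only approximately 1/m, so an offset fixed at log(m) over-corrects somewhat. This stands, and it calls for a sensitivity analysis.

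**Conclusion.** The point holds in conditional form. By the article's own rules, selection falls approximately as 1/(number of eligible residents): a ratio of 4 for 2- versus 8-person households, or 3.0 to 3.6 with 50% to 70% consent and same-house replacement. The controls therefore do not represent the person-based study base.

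The household-size OR is biased whatever the household distribution, provided sizes vary within villages. In the assumed scenario it is about 1.21 per extra member when the truth is 1.00. Other odds ratios are biased only as far as the exposure varies with household size within villages. For child versus adult the null value ranges from 1.00 (no gradient) to about 1.2–1.7 (larger households hold more children). These sizes rest on assumed distributions and are illustrations, not estimates for Sabah.

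A reader might also infer that entering household size as a covariate is enough. It is not, because the household-size coefficient itself stays biased. Nor does the problem invalidate controls already enrolled: they remain usable wherever the resident count was kept or can be recovered.

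**What to change.** - **Field selection:** keep it as it is.
- **Data:** retain the number of eligible residents for every control household, where residents are already numbered for the draw. Obtain the same count for every case household, since case homes are visited. Recover counts for participants already enrolled.
- **Conditional logistic models:** include log(number of eligible residents) as an offset, coefficient fixed at 1, for every member of the matched set. Household size may be added as an exposure, but it does not replace the offset.
- **Unadjusted results:** weight controls by the resident count in the Mantel-Haenszel odds ratios, the t and Mann-Whitney comparisons and the descriptive tables. Alternatively, take crude odds ratios from the conditional model with the offset, which is simpler.
- **Sensitivity analysis:** repeat with offset log{m/[1 − (1 − p)^m]} over plausible consent rates p, to allow for same-house replacement of refusals.
- **Text:** qualify the statement under Community controls to say that controls are drawn by household and represent persons only after this correction.

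The cost is one count per household, one offset term and some weighted tables. Intervals will be slightly wider because the weights are unequal.
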